### Measures

Additional information on measures of implementation and clinical effectiveness is presented in Tables 1 and 2, respectively.

**Table 1 Tab1:** Implementation outcomes

Outcome variable(s)	Measure(s) and data collection procedures	Data source and reporter (when applicable)
Stakeholders: acceptability, feasibility, appropriateness, and sustainability	(1) Select scales of the Annual Survey of Evidence-Based Programs [113] (*α* > .75)	Survey (ST)
	(2) FCU4Health Stakeholder Survey: 11 open-ended questions, adapted from the Treatment Acceptability Rating Form, related to the relevance of the FCU4Health for obesity management, barriers and facilitators of the delivery of the program, and feasibility of this program from the perspective of stakeholders	
	(3) Program Sustainability Assessment Tool [114]: 8 domains (e.g., funding stability, organizational capacity) with 5 items each (e.g., “The program has sustained funding”) are rated on a 7-point Likert scale (1 = little or no extent, 7 = a very great extent) (*α* = .88)	
Caregivers: acceptability and appropriateness	(1) FCU4Health Caregiver Acceptability Interview, designed for and used in our pilot feasibility trial [50], consists of 11 open-ended questions pertaining to the relevance of the program components to the family’s efforts to manage weight, the acceptability of the program and its components, and the barriers and facilitators of participation	Interview (CG)
	(2) Treatment Acceptability Rating Form-Revised Short [115–117], adapted for FCU4Health: 10 items (e.g., “How likely is FCU4Health to make permanent improvements in your child’s health behaviors?”) rated on a 7-point Likert scale (1 = not at all, 7 = very) (*α* = .92) [115]	Survey (CG)
Reach	1- or 2-month sampling period to more closely approximate the number of families that require a service at any given point [63]	EHR data
Family service participation	(1) FCU4Health activities checklist (FACL) [118] (see description in the “Methods” section)	Administrative data and Survey (CO)
	(2) Community Resources: Engagement and Adequacy (CREA): adapted from an existing care coordination measure to assess the extent to which families engaged in community resources (e.g., emergency care, well-child visits, recreational and nutrition programs, mental healthcare, school services, financial services) and if help was needed to obtain the resource and whether those resources met their needs. Response options are as follows: “I didn’t need help”; “I needed help, but didn’t find it”; “I tried this, but it didn’t work”; “I’m still getting help”; and “I got help, and it worked”	Survey (CG)
	(3) Dosage of Engagement in Community Resources (DECR) [119]: created for this study to assess the amount of time spent in activities to support health behaviors assessed by asking the number of times among 7 response options (e.g., “once a month,” “2–3 times a week,” “2 times every day”) and then the duration of each instance of teach activity using a drop-down menu of min (e.g., 30) to h (e.g., 1, 3, and 8 h or more)	
Fidelity	(1) COACH observational rating system [54]: 5 dimensions of observable in-session coordinator skills: conceptual accuracy; observant and responsive to the families’ contexts and needs; actively structures session to optimize effectiveness; carefully teaches and provides corrective feedback; hope and motivation are generated. Each dimension contains exemplars (prescribed behaviors) and non-exemplars (proscribed behaviors) and is rated on a 9-point scale: 1–3 (needs work); 4–6 (competent work); 7–9 (excellent work) (ICC ≥ .73) [120]. Variability in fidelity ratings to feedback sessions have been associated with long-term changes in parenting skills and child behavioral outcomes [53–55]	Observational
	(2) Automated coding of fidelity is being developed within this study (aim 2b)	Automated coding
Costs and health economics	(1) Cost capture survey [57]	Survey (ST)
	(2) FCU4Health activities checklist (FACL) [118] (see description in the “Methods” section)	Survey (CO)
	(3) Electronic budgets	Administrative data
	(4) Health plan claims data	Administrative data

*CG* caregiver, *CO* FCU4Health coordinator, *ST* stakeholder, *EHR* electronic health record

**Table 2 Tab2:** Clinical effectiveness and related child and family outcomes

Outcome variable(s)	Measure(s) and data collection procedures	Data source and reporter (when applicable)
Child weight and body composition	Portable electronic scale (Tanita SC-331SU) approved by the FDA for BMI and body composition in children (ages 5 to 18) and adults. Child BMI is standardized by sex and age according to the CDC growth reference data for children [121]	Anthropometric
Child dietary habits	NHANES Dietary Screener Questionnaire [122]: 9-point scale (0 = never, 8 = 6 or more times per day) to rate 3 items about fruit, vegetable, and fast-food choices (e.g., “In the past month, how often did you eat fruit?”) and 3 items regarding sugar-sweetened beverage choices (e.g., “In the past month, how often did you drink regular soda that contained sugar?”)	Survey (CG)
Family health routines and health behaviors	(1) Family Health Behaviors Scale [123]: 24 items rated on a 5-point scale (0 = almost never, 4 = nearly always; e.g., “I participate in physical activity with [child name]; [child name] sneaks food”). Caregiver ratings on this scale are sensitive to change and have been shown to predict child weight classification	Survey (CG, CH)
	(2) Sleep parenting routines: 6 items on a 5-point scale (0 = almost never, 4 = nearly always; e.g., [child name] goes to bed at about the same time each night). Items developed from existing measures, such as the Brief Infant Sleep Questionnaire [124]	
	(3) Media parenting routines: 6 items on a 5-point scale (0 = almost never, 4 = nearly always; e.g., “I keep track of [child name]’s screen-time”) and a single question on h per day of media use. Items were drawn from published studies and measures [125]	
Parenting and family management skills	Questionnaires encompass 3 domains of parenting and family management skills: (1) positive behavior support, (2) relationship quality, and (3) monitoring and limit setting. Each of these measures has been used in previous FCU trials and was found to have adequate reliability, internal consistency, and sensitivity to change	Survey (CG, CH)
	Caregiver: 5-point scale (0 = never, 4 = very often) on the domains of incentives and encouragement (4 items; e.g., “Gave [child name] a hug, kiss, or kind word”) [126]; proactive parenting (7 items; e.g., “Plan for ways to prevent problem behavior”) [127], parent–child conflict (10 items; e.g., “[child name] gets angry at me easily”); family conflict (5 items; e.g., “We got angry at each other”) [126]; quality time (6 items; e.g., “Involve [child name] in household chores”) [127], parent warmth (5 items; e.g., “If upset, [child name] seeks comfort from me”) [128]; family routines (7 items; e.g., “Check to see if [child name] has homework”); limit setting (7 items, e.g., “Speak calmly with [child name] when you were upset with him/her”), negative parent behavior (5 items; e.g., “Criticize [child name]”) [127]; and a single question on h per day of unsupervised time	
	Child: 4 items on incentives and encouragement (e.g., “Praised you or complimented you for something you did well”), using a 5-point scale (0 = never, 4 = very often); 4-item questionnaire on family conflict (e.g., “I got my way by getting angry”), using a 7-point scale (0 = never, 6 = 8+ times) [126]	
	Family interaction task (FIT) observational coding system [129]: the recorded family interactions are scored for caregiver(s) behaviors in the domains of relationship quality, positive behavior support, and monitoring and limit setting, as well as demonstrated knowledge of children’s health behaviors (e.g., age-appropriate physical activity duration and dietary guidelines). Child behaviors and emotional adaptation are rated. Each domain is rated for parent’s skill/knowledge on a 5-point scale (1 = low, 5 = high) for each interaction task independently	Observational
Child self-regulation	Caregiver: 13-item survey (e.g., “[child name] is able to resist laughing or smiling when it isn’t appropriate”) adapted from the Children’s Behavior Questionnaire [130], using a 5-point scale (1 = almost always untrue, 5 = almost always true)	Survey (CG, CH)
	Child: 16-item questionnaire (e.g., “I pay close attention when someone tells me how to do something”) adapted from the Early Adolescent Temperament Questionnaire [131], using a 6-point scale (1 = always untrue, 5 = always true)	
Weight-related stigma	Perception of Teasing Scale [132]: children will use a 5-point scale (1 = never/not upset, 4 = very often/extremely upset) to rate the frequency of 3 events pertaining to weight-related stigma and describe their level of distress associated with these items (e.g., “People made fun of you because you were heavy”; “How upset does this make you?”)	Survey (CH)
Body image	Body Image Scale for Children: a pictorial scale using body pictures representing standardized percentile curves of BMI for boys and girls, separately; good reliability and evidence of validity with children aged 7 to 12 [133]; proxy for satisfaction and a measure of potential adverse effects of participation in the program/study	Survey (CH)
Quality of life	Pediatric Quality of Life Inventory [134]: 23 items in four categories: physical functioning, emotional functioning, social functioning, and school functioning	Survey (CG, CH)
	Caregivers: 5-point scale (0 = never, 4 = almost always) to rate items (e.g., “[child name] feels afraid or scared”; “[child name] gets along with other children”)	
	Children: 3-point scale (0 = not at all, 2 = somewhat, 4 = a lot) to rate items (e.g., “It is hard for me to run”; “It is hard for me to pay attention in school”) adjusted for 2 age groups: 5–7 years old and 8–12 years old	
Satisfaction with care	(1) Family Check-Up Caregiver Service Satisfaction Survey: 9 items rated on a 4-point scale (0 = strongly disagree, 4 = strongly agree) adapted from the Client Satisfaction Questionnaire [135] to be specific to parent training programs. This was developed for use with the original FCU conducted in community mental health clinics [89] (*α* = .95) in that trial	Survey (CG)
	(2) Parent Experience of Assessment Survey (PEAS) [136]: 3 of the 5 subscales (parent–coordinator collaboration, systemic awareness, and negative feelings) with 15 total items rated on a 5-point scale (1 = strongly disagree, 5 = strongly agree) (*α* > .75)	
Child adjustment	Strengths and Difficulties Questionnaire [137]: caregivers and children rate 5 items each on a 3-point scale (0 = not true, 1 = somewhat true, 4 = very true) on the conduct problems (e.g., “I/[child name] often lose(s) temper”), hyperactivity (e.g., “I am/[child name] is constantly fidgeting or squirming”), pro-social behavior (e.g., “I am/[child name] is considerate of other people’s feelings”), and emotional problems (e.g., “I am/[child name] is often unhappy, depressed, or sad”) subscales	Survey (CG, CH)

*CH* child, *CG* caregiver, *CO* FCU4Health coordinator, *ST* stakeholder, *EHR* electronic health record

#### Implementation

To assess the *acceptability*, *feasibility*, *appropriateness*, and *sustainability* of each component of the FCU4Health (e.g., training, program costs, content, delivery), an agency stakeholder battery will be electronically administered to at least 30 agency stakeholders (approximately ten from each agency) at two times during the study: 4 months into the FCU4Health delivery and when all families enrolled in the study complete the entire 6-month FCU4Health protocol. Families in the FCU4Health arm will rate the acceptability and appropriateness of the program via an electronically administered survey at months 6 and 12. Additionally, 20% of families in the FCU4Health arm will be randomly selected and interviewed by study staff via phone.

Study enrollment and participation data will be used to evaluate the *reach* of the program in each agency by tracking both the proportion of eligible families referred to the study and the number randomized to the FCU4Health condition that engage in the program compared with the total number of eligible families [63].

We will assess the *fidelity* of coordinators to the FCU4Health using an established observation rating system that defines high-quality care and was associated with clinical improvement in studies of the original FCU [53, 54]. A trained coding team will code video or audio recordings of the first FCU4Health feedback session from every family (*N* = 200), and a subset of 80 families will be randomly selected at study entry, balanced by coordinator, for longitudinal coding of all three FCU4Health feedback sessions to assess drift (*N* = 160 additional sessions). In addition, we will develop an automated coding system based on an existing, validated automated coding system for motivational interviewing. Automated fidelity coding will be built from previous methodologies developed for coding fidelity to MI (presence of complex reflections, open-ended questions) [56, 64, 65] and family interventions [66, 67]. Machine-generated fidelity codes have been found to be reliable with human coding across multiple studies [56, 64–66, 68, 69]. Initial algorithm training will use existing FCU feedback session recordings and the FCU fidelity codebook. Automated coding involves a computational “pipeline” of both speech signal processing and machine learning of the audio recordings of the conversations during the sessions, including (1) voice activity detection, (2) diarization (i.e., how many speakers are in session and when is each talking?), (3) role identification (i.e., who is the provider?), (4) automatic speech-to-text transcription, and (5) machine learning models to predict fidelity codes, using lexical (i.e., words) and paralinguistic features as inputs.

*Cost* data collection is multi-method in order to perform analyses from multiple perspectives (e.g., agency, payor, family). Study staff report activities weekly on an electronically administered survey. FCU4Health coordinators complete a brief survey after each contact with study families (in the intervention arm) to capture the staff involved and the number of hours spent. Electronic budgets track program spending and will be used to prospectively separate costs associated with implementation from those specifically related to research (e.g., participant reimbursement, data analysis software), start-up (e.g., training), and ongoing costs (e.g., consultation with FCU4Health developers, technical assistance, travel for home visitation). At each assessment, families will be asked to provide a release for the study team to obtain health plan claims data, which will be used to identify relevant health services utilization and associated costs.

Critical to the study’s implementation aims, such as the calculation of reach and cost, is the careful tracking of participation in the various components of the program. Using methods developed and tested in previous trials, the FCU4Health coordinators and other agency staff will track all family contacts and record the delivery location, travel time, details of participating family members, the type of the FCU4Health session, content areas covered, and referrals. At each assessment, caregivers will report on their engagement in community resources, how well these resources met their needs, and the amount of time spent in activities to support health child and family behaviors.

#### Effectiveness

At each assessment, the child and caregiver(s) will be weighed using a portable electronic scale. *BMI* is the primary study outcome because it indicates cardiometabolic disease progression [70–72]. However, improvement in *body composition* in the absence of weight loss can indicate a healthy change in the ratio of fat to lean muscle, which often accompanies significant changes in diet and physical activity and results in metabolic improvement with enduring benefits [73, 74]. At each assessment point, caregivers and children report on *health-promoting family behaviors*; *mealtime, sleep, and media routines*; *child and family physical activity habits*; *child food and beverage choices*; and *use of community support services*. The FITs are used for observational assessment of parenting and family management skills using the validated Coder Impressions Inventory [75] (Dishion T, Hogansen J, Winter C, Jabson J. The coder impressions inventory, unpublished manual). Although not central to our aims, we will also assess several other constructs related to pediatric obesity: *weight-related stigma*, *body image*, *quality of life*, *child behavioral and emotional adjustment*, and *caregiver satisfaction with services*.

### Data analysis

#### Overview

Analyses focus on implementation data from the families randomized to the FCU4Health. Data from families receiving services as usual will be used in aims 2b and 3. Before data analysis, we will test the psychometric properties (i.e., distribution, reliability) of the measures, conduct a sequence of nested multiple-group confirmatory factor analyses [76] to ensure measurement invariance across language and ethnicity, and apply state-of-the-science data reduction techniques (confirmatory factor analysis, weighted regression scores) by creating multi-indicator, multi-informant construct variables when applicable. These techniques improve measurement properties and result in fewer contrasts, reducing type I error [77]. We expect the attrition rate across waves to be 10–15% based on retention rates for local studies with highly mobile, hard-to-track samples [78, 79]. We will adjust for missing data due to attrition using multiple imputation [80] and full information maximum likelihood [81]. We will perform sensitivity analyses to check the non-response mechanism [82] and attrition analyses to detect differential attrition rates and attrition by group interaction on sociodemographic and pretest variables that may pose a threat to the validity or the equity of the findings [83]. When missingness is not ignorable, we will use complex models to obtain parameter estimates [84]. To estimate power, we used Optimal Design [85] and Monte Carlo simulations in Mplus [84] and referred to relevant publications. All power analyses used 1 − *β* = .80 and *α* = .05 using two-tailed tests. For mediation models, we applied simulation in Mplus for estimating the power of path coefficients and referred to a work by Fritz and MacKinnon [86] for examining significance of mediation effects.

For qualitative data analysis, stakeholder and caregiver interviews and CAB discussions will be audio recorded, transcribed, and then coded using a directed content analysis approach [87] by using existing theory, prior results, and empirical frameworks to develop a coding scheme. Codes will be refined using a subsample of interviews, and then a team of trained coders will code full transcripts. Twenty percent of interviews will be double coded in order to calculate reliability [88]. Disagreements in coding will be resolved via consensus.

#### Aim 1

Results of the adaptation activities are largely descriptive and involve the use of qualitative data from the CAB small group discussions to describe the process and content of adaptations to the program during the course of the trial.

#### Aim 2

In addition to the specific outcomes in aims 2a–2c, we will compare the two arms on stakeholder and caregiver acceptability using repeated-measures analysis of variance (ANOVA) to analyze scores of approximately 30 stakeholders across two time points. We have sufficient power to detect a medium effect for this analysis (*f* ≥ .32). Concerning the variance of caregiver acceptability ratings between groups or over time, we have sufficient power to detect a medium effect (*f* ≥ .28). Latent growth curve (LGC) analyses will be used to determine group differences in the trajectory over time. The estimated power for this analysis is *β* = 0.12.

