**Methods:**

This (type II) hybrid effectiveness–implementation randomized trial tests the Family Check-Up 4 Health (FCU4Health) program, which was designed to target health behavior change in children by improving family management practices and parenting skills, with the goal of preventing obesity and excess weight gain. The FCU4Health is assessment driven to tailor services and increase parent motivation. A sample of 350 families with children aged 6 to 12 years who are identified as overweight or obese (BMI ≥ 85th percentile for age and gender) will be enrolled at three primary care clinics [two Federally Qualified Healthcare Centers (FQHCs) and a children’s hospital]. All clinics serve predominantly Medicaid patients and a large ethnic minority population, including Latinos, African Americans, and American Indians who face disparities in obesity, cardiometabolic risk, and access to care. The FCU4Health will be coordinated with usual care, using two different delivery strategies: an embedded approach for the two FQHCs and a referral model for the hospital-based clinic. To assess program effectiveness (BMI, body composition, child health behaviors, parenting, and utilization of support services) and implementation outcomes (such outcomes as acceptability, adoption, feasibility, appropriateness, fidelity, and cost), we use a multi-method and multi-informant assessment strategy including electronic health record data, behavioral observation, questionnaires, interviews, and cost capture methods.

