#### Implementation strategies and service delivery sites

The delivery model used by a given practice depends upon their programmatic, fiscal, and resource characteristics and needs [48]. Several approaches for the delivery of behavioral health services in primary care settings have been described [49]. In this trial, we partnered with three pediatric primary care agencies that serve high rates of low-income, ethnic minority families (about 60–65% Latino; 10% African American; 5–8% American Indian). Because pediatric primary care offices often do not have integrated behavioral health, arm 1 uses a strategy of coordinated care between primary care and an external behavioral health provider. We partnered with a large outpatient general pediatrics clinic associated with a children’s hospital. We also partnered with two agencies that are part of the nationwide network of 1250 Federally Qualified Health Centers (FQHCs). A feature of FQHCs is the integrated care model that typifies the medical home. In arm 2, we will test an integrated/co-located model of care. The FQHC network is crucial for embedding a family-centered approach to care because it serves youth and families at high sociodemographic risk and is intended to integrate services to reduce barriers and improve care. Partnering with these provider sites afforded the opportunity to compare FCU4Health implementation under two different real-life service delivery models. In both arms, behavioral health consultants are responsible for delivering the FCU4Health and coordinating care with other support services and resources.

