#### Clinical effectiveness of the FCU4Health

Within the two implementation strategy arms, eligible families are randomized to receive either the FCU4Health or clinic services-as-usual plus community program information (see “Methods”). Primary clinical outcomes are child BMI and body composition. Secondary outcomes, hypothesized to mediate effects of the intervention on primary outcomes, are lifestyle behaviors (diet and nutrition, physical and sedentary activity, sleep), child self-regulation, and family management practices.

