## Methods

### Study aims

#### Aim 1

Aim 1 was to finalize the adaptation of the FCU4Health, which was initially adapted and piloted in pediatric primary healthcare [50], based on input from a community advisory board (CAB) and partner clinics.

#### Aim 2

Aims 2 was to evaluate the effects of two delivery strategies: integrated/co-located care and coordinated care with referral. Using a mixed-methods approach applied to Proctor et al.’s [51, 52] taxonomy, we will evaluate the process of implementing the FCU4Health to inform, taking the program to scale.2a. Evaluate fidelity over time to the FCU4Health using a validated observational rating system [53–55] and develop and test an automated fidelity coding system [56].2b. Employ behavioral intervention costing methods [57] to evaluate the costs of installing and delivering the FCU4Health and conduct a cost–benefit analysis to evaluate the monetary benefits of program effects.2c. Develop a plan to support scale-up and sustainment in collaboration with our CAB.

#### Aim 3

Aim 3 was to use pragmatic trial principles to test program effects on primary and secondary outcomes. Intervention effects on proximal outcomes will be tested as mediators on the distal outcomes of child BMI and body composition.

#### Aim 4

Aim 4 was to carefully track utilization in each aspect of the program, gather data concerning family’s service delivery preferences and satisfaction, and test a model of program implementation where family engagement mediates the relation between fidelity and clinical outcomes [58].

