## Discussion

Similar to some previously published study protocols in this journal, our type II hybrid effectiveness–implementation trial blends pragmatic trial and implementation science frameworks. However, our protocol is somewhat unique to the hybrid trial design described by Curran et al. [46] because the two implementation strategies differ on the pragmatic–explanatory trial continuum [108] in which the integrated/co-located care arm of the trial is more pragmatic compared to the coordinated care with referral condition, which is more explanatory. However, both conditions are far more pragmatic than they are explanatory—as would be expected for a hybrid trial. This was done to speed translation given that the effectiveness of the adapted FCU4Health program was partially supported by the large existing corpus of evidence supporting the original FCU to both change the purported mediators as well as the primary child outcomes [44]. Additionally, the request for applications for the Childhood Obesity Research Demonstration Projects 2.0 indicated preference for such a design [109].

One of the primary challenges we have encountered since beginning this study relates to working with healthcare organizations. Context is always critical to implementation research, and differences are magnified when attempting to implement a complex behavioral intervention where, previously, a similar program did not exist. The partnerships between the research team and the community sites are critical for success [110], and we have been able to remain successful due to the strength of our partnership, but administrative, personnel, and other issues required extensive meetings, which protracted our planned preparation time from 6 months to nearly 12 months. Many of the issues that were raised could not have been avoided. In part, the extended time was due to variation within our partner clinics that necessitated meetings as well as continually garnering buy-in from leadership and staff that would deliver the FCU4Health.

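### Delivery strategy is not randomised and coincides with clinic (one hospital clinic v two FQHCs), so the Aim 2 comparison of acceptability on individual raters can present clinic differences as strategy effects

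*Protocol article*

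**What the plan says.** **Assignment of strategy.** The abstract describes "an embedded approach for the two FQHCs and a referral model for the hospital-based clinic". The section on implementation strategies and service delivery sites explains that "The delivery model used by a given practice depends upon their programmatic, fiscal, and resource characteristics and needs". What is randomised is the family, inside each strategy: "Within the two implementation strategy arms, eligible families are randomized to receive either the FCU4Health or clinic services-as-usual plus community program information" (Clinical effectiveness of the FCU4Health). The Discussion adds that "the integrated/co-located care arm of the trial is more pragmatic compared to the coordinated care with referral condition, which is more explanatory".

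**Purpose.** Study aims, Aim 2, is to "evaluate the effects of two delivery strategies: integrated/co-located care and coordinated care with referral".

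**Data.** Stakeholder ratings come from "at least 30 agency stakeholders (approximately ten from each agency) at two times during the study" (Measures, Implementation). Caregiver acceptability is rated only by families in the FCU4Health arm, at months 6 and 12.

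**Analysis.** Data analysis, Aim 2: "we will compare the two arms on stakeholder and caregiver acceptability using repeated-measures analysis of variance (ANOVA". It claims power for a medium effect, f ≥ .32 for about 30 stakeholders and f ≥ .28 for caregivers (between groups or over time). It then plans latent growth curve (LGC) analyses of group differences in trajectory, with a power figure of β = 0.12. The Overview sets two-tailed α = .05 and 80% power throughout. No clinic term is named under Aim 2. The only provision for site is at the end of Aim 3: a design effect is calculated and, if significant, multilevel models with site or coordinator as the cluster are used.

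**The concern.** Although the word arm is used elsewhere for treatment condition, the arms compared under Aim 2 must be the strategy arms. Stakeholders are not randomised, only FCU4Health families rate acceptability, and the Overview reserves services-as-usual data for Aims 2b and 3.

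Strategy is thus a clinic-level factor with one clinic on one side and two on the other, and it was set by the characteristics of the practices. Two problems follow. First, a difference in acceptability between the hospital and the FQHCs cannot be credited to the strategy, whatever its p-value. Second, a test that counts raters as independent uses an error term that omits clinic-to-clinic variation, so its error rate as a test of strategy exceeds the nominal 5%.

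Aim 2 is meant to inform taking the program to scale. A significant result could be read as evidence for one delivery model when it shows only that clinics differ.

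**Working it through.** **1. The stated power figures.** With N = 30 independent raters, two time points and df 1 and 28, the noncentrality is λ = f²·N·2/(1+ρ) for the arm main effect and f²·N·2/(1−ρ) for time or arm-by-time, where ρ is the within-rater correlation.
- Arm main effect at f = .32: power 67%, 56% and 50% at ρ = 0, .3 and .5.
- Time or arm-by-time at ρ = .27: λ = .1024 × 60/.73 = 8.42, power 80%.

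The article states neither ρ nor the term tested, so f ≥ .32 cannot be fully reproduced. For caregivers, f = .28 corresponds to about 100 independent raters at one time (λ = .0784 × 100 = 7.84, power 79%). All these calculations treat raters as independent. None contains a clinic component.

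**2. What clinic variation does to the arm main effect.** Take total variance 1, clinic share ICC and n raters per clinic. The hospital-minus-FQHC contrast of means has variance (1 + 1/2)·(ICC + (1−ICC)/n). An analysis of independent raters takes it to be about 1.5/n. The ratio is 1 + (n−1)·ICC. At ICC .05:
- n = 10: 1 + 9 × .05 = 1.45
- n = 67: 1 + 66 × .05 = 4.30

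**3. False-positive rate.** Inputs from the article: 1 v 2 clinics, about 10 stakeholders per agency, 200 FCU4Health families, 10–15% attrition. Assumed: the ICC, and equal caregiver numbers per clinic (200/3 = 67; 200 × .85/3 = 57; or 33 if about 100 rate, as f = .28 suggests). I simulated a two-sided 5% test of the arm main effect with no strategy effect, 200,000 trials per cell. Each cell shows the result for one rating per rater, then for the mean of two ratings with within-clinic correlation .5 between them.

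| Raters per clinic | ICC 0 | .01 | .02 | .05 | .10 |
|---|---|---|---|---|---|
| Stakeholders, 10 | 5 / 5% | 6 / 6% | 7 / 8% | 10 / 12% | 16 / 19% |
| Caregivers, 33 | 5 / 5% | 9 / 10% | 13 / 15% | 23 / 27% | 35 / 41% |
| Caregivers, 57 | 5 / 5% | 12 / 14% | 18 / 22% | 32 / 37% | 46 / 51% |
| Caregivers, 67 | 5 / 5% | 13 / 15% | 20 / 24% | 35 / 41% | 49 / 54% |

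With an overall within-rater correlation of .3, the rates at ICC .10 are about 22% for stakeholders and 58% for 67 caregivers per clinic.

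**4. Arm-by-time.** A constant clinic effect cancels in each rater's change score. Simulated at ICC .05 with 10 and 67 raters per clinic, this test stays at 5%. Clinic-by-time variation was not modelled and could raise it.

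**5. Clinic as the unit.** Three clinic means leave 1 error degree of freedom, and the critical t is 12.71. Power of 80% needs a difference of about 16.3 standard errors. At ICC .05 with one rating per rater:
- Stakeholders: SE = √(1.5 × (.05 + .95/10)) = .47 SD, so about 7.6 SD
- Caregivers, 67 per clinic: SE = √(1.5 × (.05 + .95/67)) = .31 SD, so about 5 SD

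Applying the Aim 3 site rule here would therefore leave no usable test. It would also still assume that the hospital differs from the FQHCs only in strategy and ordinary clinic variation.

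**The case against.** Several points on the other side stand.

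- A reader might infer that clinic differences will be declared strategy effects. The documents support only that they can be. No ICC is given, and for stakeholders at ICC .01–.02 the error is about 6–8%.
- A reader might infer that the whole hybrid comparison of delivery models rests on this test, or that the trial's main result is at risk. Neither is supported. Acceptability is compared in addition to the outcomes of Aims 2a–2c. Aim 2 is mixed-methods, and its sustainability component is largely descriptive. BMI and body composition are tested between randomised families within strategy arms.
- The inflated rates apply to the arm main effect only. The planned trajectory comparison is not inflated by a constant clinic effect.
- If the three clinics are treated as fixed, a test of whether their raters differ is valid for those clinics. The defect is then purely one of attribution.
- The article openly says that the model follows practice characteristics and that the arms differ in pragmatism. A fuller protocol might limit the inference further.

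The last two points do not remove the problem. The article states its aim as the effects of the strategies and fixes the test and its power. It nowhere limits the comparison to description. No later modelling choice can separate one hospital from the strategy used only there.

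**Conclusion.** The point holds. Strategy is non-randomised and coincides with clinic, so the Aim 2 contrast on acceptability cannot estimate a strategy effect. That follows from the design and needs no assumption about the ICC.

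The size of the error inflation does depend on assumptions: ICC .01–.10, equal clinic sizes, up to two ratings per rater correlated .5 within clinic, and no strategy effect. On these, the arm main effect is falsely significant about 6–19% of the time for stakeholders and about 9–54% for caregivers, against a nominal 5%. The arm-by-time test holds its level under a constant clinic effect but carries the same confounding. The consequence is confined to one implementation analysis, so this is a correction worth making rather than a threat to the trial's primary conclusion.

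**What to change.** 1. In Data analysis, Aim 2, report stakeholder and caregiver acceptability clinic by clinic at each time point, with within-clinic intervals.
2. Label the hospital-versus-FQHC contrast, both in mean level and in LGC trajectory, as descriptive and not attributable to strategy.
3. Show the difference between the two FQHCs as a rough indication of clinic-to-clinic variation. Say that it is a single difference between clinics of the same type and may understate the variation between a hospital and an FQHC.
4. Withdraw the between-strategy power statements: f ≥ .32 and f ≥ .28 as applied to the arms, and the figure for the LGC group difference.
5. In Study aims, reword Aim 2 from evaluating effects to describing implementation under two delivery strategies.

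The Aim 2a fidelity tests, the within-rater tests over time and the randomised family-level comparison stay as they are. The cost is some rewording, a by-clinic table and the removal of the power statements. Recruitment and data collection do not change. A formal p-value for strategy is given up, but three clinics cannot support a valid one.
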